## Background

Research on the effectiveness of intensive care treatment has traditionally focused on mortality [1-3]. The cumulative 12 month mortality of survivors of ICU treatment in the UK varies between 35% and 43% [4,5]. Over the five years after an ICU admission these patients also have an excess risk of death when compared to an age and sex matched population [6]

However, apart from this excess mortality, recent research has confirmed that survivors of ICU treatment continue to experience both physical [7], and psychological problems [4,8,9] for some time after discharge from ICU [7,10]. The reported prevalence of anxiety and depressive problems in ICU survivors ranges from 12% to 43% (for anxiety) [4,11], and 10% to 30% (for depression) [4,11]. Two recent reviews estimate that 5% to 64% of intensive care patients may develop either post traumatic stress disorder (PTSD) or its associated symptoms that may endure for a number of years [12,13]. However, the studies reporting on the rates of PTSD and PTSD symptoms in ICU survivors vary considerably in their case mix, demographic variables, and method and timing of PTSD assessment [12,13]. All these factors complicate comparisons between studies and limit quantitative synthesis of their findings. As a result, the extent to which the consequences of critical illness or treatments received in the ICU contribute to the prevalence of PTSD symptoms during recovery is currently poorly understood. Thus, well-designed studies are needed to determine accurate prevalence rates of PTSD in survivors of ICU treatment.

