### Sample size

The minimum target total survivor recruitment for the study would be at least 1000 survivors per year in the first year returning all questionnaires. With this sample size, the ICON study would be the largest existing prospective cohort study of long-term outcomes in ICU survivors.

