### Planned analyses

Using ICU admission as the event defining the start of follow-up, Kaplan-Meier curves will be constructed to illustrate survival. Age and sex matched control data will be requested from ONS in a 1:1 ratio with the patients in the study, and a control group Kaplan-Meier curve calculated from these data. A log-rank test will be used to determine the statistical significance of any differences noted.

It is almost certain that the ICU survivors will show a decreased longevity compared with the general population, so this initial testing will only be used to validate the study by showing similar results to previous investigations. However, as this is a non-randomised study, there are many potential sources for bias. To minimise the possibility that a difference in survival is due to confounders and not a real effect of the either illness or the ICU care, further covariate analysis will be undertaken. To determine the effects of covariates on survival, the Cox proportional hazards method will be used. The covariates included in the model will be age, sex, APACHE II predicted mortality, socio-economic status (from postcodes), geographical area (4 zones north to south based on hospital location), month of discharge, and 12 broad diagnostic categories based of the organ system involved in the acute illness. These results will be presented as a table showing the relative effects of ICU care and the covariates on survival.

The data on psychological illness (anxiety, depression and PTSD symptomatology), and quality of life will be largely descriptive and will be presented in tabular form.

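### A log-rank test against population controls can confirm only the expected direction of excess mortality; it cannot validate the study by showing results similar to earlier ICU cohorts

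*Protocol article*

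**What the plan says.** All of the following is in the Protocol article.

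- **Planned analyses, the comparison.** Kaplan-Meier curves are drawn for the cohort and for a control group: "Age and sex matched control data will be requested from ONS in a 1:1 ratio with the patients in the study". The clock is set by "Using ICU admission as the event defining the start of follow-up". Then: "A log-rank test will be used to determine the statistical significance of any differences noted".
- **Planned analyses, the expected result.** "It is almost certain that the ICU survivors will show a decreased longevity compared with the general population".
- **Planned analyses, the use of the test.** "so this initial testing will only be used to validate the study by showing similar results to previous investigations".
- **Background, the earlier results.** Two kinds are cited. One is a level: cumulative 12-month mortality of UK survivors of ICU treatment between 35% and 43%. The other is a direction, relative to the general population: "Over the five years after an ICU admission these patients also have an excess risk of death when compared to an age and sex matched". No hazard ratio is given for it.
- **Sample size.** The target is "at least 1000 survivors per year in the first year returning all questionnaires". It is not derived from a power calculation for the survival comparison.

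**The concern.** The log-rank null hypothesis is that cohort and controls have the same survival. The claim the test is meant to support is that this study resembles previous ones. These are different questions. The test uses only the survival times of the patients and of their ONS controls, so its p-value carries no information on distance from an earlier estimate.

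The protocol also expects the result before any data are seen. A check that comes out the same way for cohorts with very different mortality adds little to what was already believed. At stake is the meaning of the word validate: a significant p-value could be reported as agreement with earlier work when the size of the excess had not been compared with anything.

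**Working it through.** The article gives no alpha, hazard ratio, event count or margin for this test, so there is no stated figure to reproduce. The check asks whether the test result changes as the cohort's mortality moves across a wide range.

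**Inputs from the document**
- 1000 patients (Sample size target) and 1000 controls (1:1 ratio, Planned analyses).
- 12 months: the horizon of the cited mortality figure, and a follow-up point in every version of the schedule the article gives.

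**Assumptions, not in the document**
- Two-sided 5% test and proportional hazards.
- Control 12-month mortality of 2%, 3% or 4%.

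**Formulas**
- Hazard ratio: HR = ln(1 − p_cohort) / ln(1 − p_control).
- Expected deaths: D = 1000 × (p_cohort + p_control).
- Power (Schoenfeld): Φ(½·√D·ln HR − 1.96).

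**Two worked cells, control mortality 4%**
- Cohort 10%: HR = 0.1054/0.0408 = 2.58; D = 140; ½·√140·ln 2.58 = 5.61; power = Φ(3.65), above 0.999.
- Cohort 5%: HR = 0.0513/0.0408 = 1.26; D = 90; ½·√90·ln 1.26 = 1.08; power = Φ(−0.88) = 0.19.

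**Chance of a significant result**

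| Cohort 12-month mortality | Control 2% | Control 3% | Control 4% |
|---|---|---|---|
| 5% | 0.97 | 0.64 | 0.19 |
| 6% | 0.999 | 0.92 | 0.55 |
| 8% | 1.00 | 1.00 | 0.97 |
| 10% | 1.00 | 1.00 | 1.00 |
| 20% | 1.00 | 1.00 | 1.00 |
| 35% | 1.00 | 1.00 | 1.00 |

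Simulation of the log-rank test itself (1500 studies per cell, exponential survival, censoring at 12 months) agrees. At 10% cohort mortality it is significant in at least 99.9% of studies for all three control rates. At 5% against 4% it is significant in 18%.

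The last three rows are indistinguishable by the test. Yet with 3% control mortality they correspond to hazard ratios of about 3.5, 7.3 and 14.1. That difference in size is what a comparison with previous investigations would have to examine.

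**What an estimate would show.** The 95% half-width for 12-month mortality is 1.96·√(p(1 − p)/1000). It is 1.9 points at 10%, 2.5 at 20% and 3.0 at 35%. Intervals that narrow separate the same three cohorts clearly.

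**The case against.** The best defence is that similar results means only the same direction. The Background reports excess death against an age- and sex-matched population, and the planned test makes that same kind of comparison. On that reading the null does fit the claim. The word only also demotes the test, and the section goes on to warn of bias and to plan a Cox model. This stands in part: the test can confirm direction. But direction is what the protocol calls almost certain, so confirming it validates little.

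Other limits also stand:
- The article sets no pass/fail threshold. The Kaplan-Meier curves could be compared informally with published survival, although no such comparison is described.
- It would be wrong to say that almost any cohort passes. A small excess often does not, as the 5% and 6% rows show for 4% controls.
- The 1000 is a target for questionnaire return, not a stated size for the survival cohort. With 300 per group, 10% against 2% still gives power of 0.999, and 10% against 3% gives 0.97.
- The cited 35% to 43% refers to survivors of ICU treatment, while eligibility here requires survival to hospital discharge. Lower mortality in this study would not by itself mark the cohort as unusual.

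A reader might go further and infer that the study would be falsely declared representative, and that the error would pass into the prevalence and QALY results. The document does not support this. Representativeness is an aim, but nothing says this test checks it. The Cox model, the descriptive tables and the QALY analysis are not conditional on it.

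A named agreement margin could properly be left to an analysis plan. The use assigned to the test, however, is stated in the article.

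**Conclusion.** The point holds in limited form. The article gives the log-rank test a purpose that it can serve only as far as direction. Under the assumptions shown, it returns the same answer for 12-month mortality of 10%, 20% or 35%, so it cannot show that the cohort's mortality is close to earlier figures. The numbers depend on the assumed control mortality, alpha, proportional hazards and 1000 per group. The argument that no earlier estimate enters the test depends on none of these. The effect is confined to how the survival comparison is interpreted and reported.

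**What to change.** In Planned analyses, drop the claim that the log-rank test validates the study. Describe the test as confirming the expected direction of excess mortality.

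Add that 12-month mortality, and the hazard or mortality ratio against the matched controls, will each be reported with a 95% confidence interval. Set these beside the earlier UK estimates cited in the Background, after aligning the population (hospital survivors) and the time origin. Base any statement of similar results on that comparison, not on the p-value.

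The cost is a change of wording and a little extra analysis of data already planned from ONS, with no new patients or procedures. The small downside is that the study may have to report that its mortality differs from that of earlier cohorts.

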### Aims and objectives of the study

The ICON study aims to:

Define the longer-term outcomes of a large, representative sample of survivors of adult, general ICU care in the UK quantitatively in terms of their survival, HRQoL and psychological morbidity 3, 6 and 12 months after ICU discharge.

Compare the mortality of survivors of adult, general ICU care with age-, sex- and condition-matched populations of people who have not experienced ICU care.

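### The adjusted ICU-versus-control mortality contrast is a Cox relative effect with no stated horizon, in a design where proportional hazards is doubtful and the follow-up length is contradictory

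*Protocol article*

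**What the plan says.** All of the survival methods are in the protocol article under Planned analyses.

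- **Time zero:** "Using ICU admission as the event defining the start of follow-up".
- **Display:** "Kaplan-Meier curves will be constructed to illustrate survival", with a second curve for age- and sex-matched controls obtained 1:1 from national statistics.
- **Unadjusted test:** "A log-rank test will be used to determine the statistical significance of any differences noted". Its role is limited, "so this initial testing will only be used to validate the study by showing similar results to previous investigations".
- **Adjusted analysis:** "To determine the effects of covariates on survival, the Cox proportional hazards method will be used". The output is "a table showing the relative effects of ICU care and the covariates on survival". Study group is not in the covariate list, so it is this last sentence that shows the Cox model is meant to carry the ICU-versus-control contrast.

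Planned analyses gives no horizon, no division of follow-up time and no survival contrast at a named time.

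Other sections bear on this:

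- Aims and objectives asks for outcomes "quantitatively in terms of their survival, HRQoL and psychological morbidity 3, 6 and 12 months after ICU discharge".
- Outcome assessments, Procedure and Economic issues use 3, 12 and 24 months instead.
- Inclusion criteria admits only patients alive at hospital discharge.
- Background gives 35% to 43% cumulative 12-month mortality in ICU survivors and an excess risk of death over five years. It gives no time pattern and no control rate.

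**The concern.** A Cox model without time-dependent terms returns one ratio per factor. If the true ratio is constant, that number means the same at any follow-up length. If it is not, the number is a weighted average over whatever follow-up was available.

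There are two reasons to doubt constancy here. The first is built into the design: between ICU admission and hospital discharge the case hazard is zero by selection, while the control hazard is not. The second is clinical plausibility: the excess hazard may fall as patients recover, and the effect of acute severity may fade with it.

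What is at stake is interpretability. The first aim asks for survival at set times, whereas the only adjusted, quantified contrast is tied to no time. Because the protocol gives two follow-up schedules, two analysts could follow it faithfully and report materially different ratios from the same patients. Comparison with earlier studies, which the protocol intends, would also depend on matching follow-up lengths.

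**Working it through.** **Plan's own figure.** There is none to reproduce. The protocol states no hazard ratio, event count or horizon, and the target of at least 1000 survivors has no survival calculation behind it.

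**Method.** Hazards are piecewise constant. For interval mortality q over length L years, h = −ln(1−q)/L. For controls with annual mortality c, h0 = −ln(1−c). With 1:1 groups and no censoring before horizon T, the large-sample Cox log ratio β solves

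∫ from 0 to T of [h1·S1 − (h1·S1 + h0·S0)·e^β·S1/(e^β·S1 + S0)] dt = 0.

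**Check under proportional hazards.** With a constant ratio of 2 and c = 2%, the result is 2.00 at 3, 12, 24 and 60 months. There is then no dependence on horizon.

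**Step 1: death-free period (from the design).** The case hazard is zero until entry and the true ratio is 2 afterwards. Assumed: c = 2% and the length of the period.

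| Death-free period | 6 mo | 12 mo | 24 mo | 60 mo |
|---|---|---|---|---|
| 1 month | 1.67 | 1.83 | 1.92 | 1.96 |
| 3 months | 1.00 | 1.50 | 1.74 | 1.89 |

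The 3-month row applies only if the analysis is restricted to patients confirmed alive for the 3-month mailing. The bias is downward and shrinks as follow-up lengthens.

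**Step 2: falling hazard after discharge, lower-mortality scenarios (all inputs assumed).** Worked example with 6% dying in 0–3 months, 8% in 3–12 and 6% in 12–24, and controls at 2.5% a year:

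- h1 = 0.0619/0.25 = 0.2475, then 0.0834/0.75 = 0.1112, then 0.0619 per year; h0 = 0.0253.
- Interval ratios: 9.8, 4.4 and 2.4.

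| Case mortality by interval; control rate | Interval ratios | Cox at 12 mo | Cox at 24 mo | Fall |
|---|---|---|---|---|
| 6%, 8%, 6%; 2.5% | 9.8 / 4.4 / 2.4 | 5.8 | 4.1 | 28% |
| 4%, 6%, 5%; 2.5% | 6.4 / 3.3 / 2.0 | 4.1 | 3.1 | 25% |
| 10%, 10%, 7%; 1.5% | 27.9 / 9.3 / 4.8 | 14.0 | 9.5 | 32% |

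A simulation of the same scenarios with 60,000 per group gave Cox ratios of 5.6 and 4.0, 4.1 and 3.1, and 14.2 and 9.8, which are falls of 29%, 24% and 31%. The two methods agree closely.

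These scenarios imply 12-month mortality of 1 − 0.94×0.92 = 14%, 1 − 0.96×0.94 = 10% and 1 − 0.90×0.90 = 19%, well below the Background's 35–43%.

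**Step 3: the same calculation at the Background's mortality.** Case 12-month mortality is 35% or 43%. Assumed: controls at 1%, 2% or 4% a year; a ratio after year 1 of 1.5 or 3; first-year hazard either even or 70% in the first 3 months.

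- Example (35%, controls 2%, 70% early, later ratio 1.5): 59.7 at 3 months, 21.5 at 12, 11.7 at 24 and 5.8 at 60. With an even first-year hazard: 21.3 at 12, 11.6 at 24 and 5.8 at 60.
- All combinations: 10.6 to 56.2 at 12 months, 6.2 to 29.9 at 24 and 3.6 to 14.1 at 60. The fall from 12 to 24 months is 34% to 48%.

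The even and front-loaded patterns give almost the same answers at 12 and 24 months. The fall is therefore driven by the assumed lower ratio after year 1.

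**Step 4: is a falling hazard consistent with the document?** If the first-year rate persisted for five years, 1 − 0.65^5 = 88% to 1 − 0.57^5 = 94% would be dead. The document gives no five-year figure, so this is indirect support only.

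**The case against.** The strongest reply is that naming the Cox method does not rule out checks of proportional hazards, time-varying terms or a horizon, all of which normally sit in an analysis plan that is not shown. That stands as far as it goes: a missing diagnostic check is not the point here. The point is that the protocol has chosen the form of the result, a table of relative effects, alongside a time origin that breaks proportionality and two conflicting follow-up schedules.

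A reader might also infer more than the document supports:

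- **That excess mortality is known to be concentrated early.** No section says so. Background gives a 12-month range and a five-year excess, without an early/late split. It remains an assumption.
- **That the log-rank test is wrong.** It remains a valid test of no difference when hazards are not proportional, losing only power, and the protocol limits it to validation.
- **That survival at set times is absent.** Kaplan-Meier curves for both groups show it. What is missing is a quantified contrast at those times and a horizon for the Cox effect.
- **That the Cox ratio is the headline result.** Nothing gives it that status; its stated purpose is to deal with confounding.
- **That the direction of error is known.** The death-free period pulls the early ratio down, while a falling post-discharge hazard makes it high early. The net effect cannot be settled from the document.

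**Conclusion.** The concern holds in limited form and is worth correcting. The documents establish three things: a Cox relative effect with no horizon, a time origin that precedes entry and so makes the case hazard zero at first, and follow-up ending at 12 months in one section and 24 in others. Given these, the single ratio is interpretable only if hazards are proportional, and the design itself makes that untrue near time zero.

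The size rests on assumed control mortality, post-discharge pattern and later ratio. Moving from 12 to 24 months lowers the ratio by about 24–31% in the lower-mortality scenarios (25–32% as large-sample limits) and by about 34–48% at the Background's mortality. The Background range describes survivors of ICU treatment, whereas the cohort must also survive to hospital discharge, so it may not apply to the cohort directly. If the post-entry ratio is in fact constant, only the death-free period remains: with an assumed month and a true ratio of 2, the estimate is 1.83 at 12 months and 1.92 at 24.

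**What to change.** Amend Planned analyses as follows:

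1. Start the survival clock at hospital discharge, with each control's follow-up starting on the matched patient's discharge date. Alternatively, keep ICU admission as the origin and use delayed entry at discharge.
2. Reconcile the follow-up times between Aims and objectives and the Outcome assessments, Procedure and Economic issues sections, and state the horizon of the survival analysis.
3. Report Kaplan-Meier survival in each group, and the difference with a 95% confidence interval, at each reconciled assessment time.
4. Give ICU-versus-control hazard ratios for the intervals between those times, and allow the severity effect to vary over the same intervals.
5. Report any overall Cox ratio only as a secondary average, with its follow-up length beside it.
6. Keep the log-rank test in its validation role, on the corrected time scale.

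The case and control survival data are already planned; the controls need an index date. The cost is revised wording, a little more programming and wider confidence intervals for interval-specific ratios than for one pooled ratio. The changes do no harm if hazards prove proportional.

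### The Cox model as listed cannot give the promised adjusted effect of ICU care, because APACHE II risk and acute-illness category have no values for age- and sex-matched population controls

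*Protocol article*

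**What the plan says.** All of this is in the protocol article.

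- **Controls** (Planned analyses): "Age and sex matched control data will be requested from ONS in a 1:1 ratio with the patients in the study". The same section describes the comparator as the general population: "It is almost certain that the ICU survivors will show a decreased longevity compared with the general population".
- **Purpose of the Cox model** (Planned analyses): "To minimise the possibility that a difference in survival is due to confounders and not a real effect of the either illness or the ICU" (the quote stops one word short; ICU care is meant). The log-rank comparison that comes before it is kept only as a check against earlier studies.
- **Covariates** (Planned analyses): the list opens with age and sex and continues with "APACHE II predicted mortality, socio-economic status (from postcodes), geographical area (4 zones north to south based on hospital location), month of discharge"; it ends with twelve diagnostic groups defined by the organ system of the acute illness. No ICU-versus-control indicator is in the list.
- **Output** (Planned analyses): "These results will be presented as a table showing the relative effects of ICU care and the covariates on survival".
- **Aim** (Aims and objectives of the study): the mortality comparison is to be with "age-, sex- and condition-matched populations of people who have not experienced ICU care".
- **Data sources**: APACHE II and ICU diagnosis are baseline data on study patients (Trial recruitment and baseline measurements). Clinical data arrive by download from ICNARC (Data collection). No clinical data source is named for controls.

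**The concern.** An effect of ICU care on survival needs people with and without ICU care in one model, and every covariate in that model needs a value in both groups. APACHE II predicted mortality scores an ICU admission, and the twelve categories classify the illness that led to it. A person drawn from the general population to match on age and sex has neither. The document does not state outright that controls lack these fields. That is an inference from a control request limited to age and sex, with no clinical source attached.

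The mortality comparison is one of the study's two stated aims. Because the log-rank test serves only as validation, the Cox model is the sole analysis meant to separate confounding from a real effect of illness or ICU care. If the listed model cannot supply that effect, either the table cannot be produced or it will hold a coefficient whose value depends on how the controls were coded.

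**Working it through.** The plan gives no figure on this point, so there is none to reproduce. The check is whether the listed model can identify an ICU effect under each way of fitting it. Write *I* for the ICU indicator (1 = patient, 0 = control), *A* for APACHE II predicted mortality and *D1* to *D12* for the diagnostic categories.

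**1. Complete cases.** Controls have no *A* and no *D*, so all are dropped. *I* equals 1 for everyone left, its variance is 0, and no ICU coefficient exists.

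**2. A not-applicable diagnosis level for controls.** Every patient has exactly one category and every control has none, so *D1* + ... + *D12* = *I*. The indicator plus 12 dummies make 13 columns of rank 12, so *I* is exactly collinear with the diagnosis terms.

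**3. Controls coded as zero or as the reference category.** The model fits. With *A* centred at *c* in patients and reference diagnosis *d*, exp(coefficient of *I*) is the hazard ratio against controls for a patient with diagnosis *d* and predicted mortality *c*. Moving the centre from *c1* to *c2* multiplies it by exp[γ(*c2* − *c1*)], where γ is the log-hazard slope for *A*. Changing the reference diagnosis multiplies it by the ratio of the two diagnosis effects.

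A simulation shows the size. All its parameters are assumptions: 1000 patients and 1000 age/sex-matched controls; 2 years of follow-up; baseline hazard 0.08 per year; age slope 0.04 per year; γ = 2; diagnosis effects evenly spaced from −0.6 to +0.6 on the log scale; ICU hazard ratio 1.5 at average severity and diagnosis. ICU hazard ratio from one data set:

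| Reference diagnosis | *A* centred at 0 | at 0.28 (the mean) | at 0.5 |
|---|---|---|---|
| lowest-risk | 0.31 | 0.63 | 1.08 |
| middle | 0.49 | 1.00 | 1.72 |
| highest-risk | 1.42 | 2.90 | 4.99 |

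Moving the centre from 0 to 0.28 multiplies each row by about the same factor: 0.63/0.31 = 2.03, 1.00/0.49 = 2.04, 2.90/1.42 = 2.04. The nine numbers are therefore one fitted model read at nine reference points.

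**4. Patients only.** Every covariate is available, but there is no unexposed group and so no ICU effect to report.

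**5. Shared covariates only.** With *I*, age, sex and socio-economic status, the same data gave an ICU hazard ratio of 1.50. This shows that a patients-versus-controls contrast can be estimated. It is not adjusted for severity or diagnosis, so it combines the illness with the ICU care.

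**Weaker examples.** From "month of discharge, and 12 broad diagnostic categories based of the organ system involved in the acute illness" only the diagnostic part is decisive. A control could take the matched patient's index month, and a zone could be assigned from residence. The plan says neither, and it defines zone by hospital, but these two covariates do not by themselves defeat the model.

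**The case against.** **The Cox model may be meant for patients only.** It is introduced as a way to find covariate effects on survival, and the list contains no ICU indicator. On that reading it is estimable. This stands as a reading of the covariate list, but the stated purpose and the promised ICU-care row are then wrong, so the section still needs correcting.

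**A joint model can be fitted.** Dropping the redundant indicator leaves 12 category-versus-control contrasts, and APACHE II can be nested within patients and centred. This is correct, and the coding is the kind of detail an article leaves to a fuller document. But what comes out is a survivor-versus-population contrast at a chosen severity and diagnosis. No coding turns it into an effect of ICU care adjusted for severity, because no control has a severity value.

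**Condition-matched controls would help.** They could supply a diagnosis and a discharge month, though not an ICU severity score on the same basis. Planned analyses does not request them.

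Three stronger readings are tempting, and the documents do not support them:

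- *That the coding biases the hazard ratio by a known factor.* With an assumed mean risk of 0.2 to 0.3 and slope of 2 to 4, exp(2 × 0.2) = 1.49 and exp(4 × 0.3) = 3.32, so a ratio of 4 would read as 4/1.49 = 2.68 or 4/3.32 = 1.20. That compares mean severity with zero severity in one model. It is a change of reference under assumed inputs, not bias.
- *That severity and diagnosis are part of the exposure and not confounders.* For an effect of ICU care as such they are central confounders. They belong to the exposure only if it is redefined as critical illness plus ICU care.
- *That no mortality comparison is possible.* The age/sex-matched Kaplan-Meier and log-rank comparison remains, and so does the shared-covariate model in step 5.

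**Conclusion.** The point holds for APACHE II predicted mortality and the acute-illness categories, and those two are enough. Under none of the four ways of fitting the listed model does it yield the severity-adjusted ICU-care effect that the table promises. This is a conflict between the plan's stated purpose, covariates and output, not an omitted detail. Steps 1, 2 and 4 need no numerical assumption. They rest only on the inference that age/sex-matched ONS controls carry no ICU severity score or acute-illness category. The range 0.31 to 4.99 illustrates step 3 for one simulated data set with assumed parameters and should not be quoted as an expected error.

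The consequence is confined to the mortality aim. The psychological and quality-of-life results are planned as largely descriptive and are unaffected. What the study can conclude about mortality is how ICU survivors fare against the general population and, separately, which patient characteristics predict death among them. The aim's condition-matched comparison is a related conflict, since Planned analyses matches on age and sex only.

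**What to change.** Replace the single Cox model with two.

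- **Model A, patients plus controls.** Include an ICU-survivor indicator, respect the age/sex matching, and adjust only for covariates actually held in both groups. Postcode deprivation, area of residence and index calendar month are candidates if ONS supplies or allows them; the article does not say that it does. Report the result as the survivor-versus-population mortality contrast for critical illness and ICU care combined.
- **Model B, patients only.** Include age, sex, APACHE II predicted mortality, diagnostic category, socio-economic status, discharge month and zone. Report it as a prognostic model with no ICU-care row.

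Delete the claim to estimate an adjusted effect of ICU care, and present two tables in place of one. Reconcile the condition-matched comparison in the aims with the age/sex-only control request, by changing one or the other.

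The cost is one rewritten paragraph and one extra model fit on the same data, provided the aim is brought into line with the existing control request; obtaining condition-matched controls would need a different request. The study gives up a severity-adjusted ICU-care effect, which this design cannot deliver. Model A does not settle a separate question: follow-up starts at ICU admission although eligibility requires survival to hospital discharge.
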